### Control group conditions/usual care

The primary care nurses in the control group will not have access to the implementation strategy. They will be offered an opportunity to join the training program at the end of the study. The nurses will be instructed to administer usual care consistent with current diabetes guidelines. These guidelines state that, in usual care, the GP pays attention to complaints, glucose regulation, current cardiovascular risk, and the early identification of complications. Patients without complaints and with good metabolic regulation will be invited to check-ups every 3 months. Once a year, the GP will pay extra attention to specific items noted during the consultations[18].

#### Three-monthly check-ups

At the check-up, the GP will ask about well-being, symptoms that indicate hyperglycemia or hypoglycemia, complications in diet and exercise counseling, and medication. The GP will note the patient's weight. The fasting blood glucose value will also be determined every 3 months[18].

#### Annual check-ups

The annual check-up will be extensive. The GP will ask about eye complications, cardiovascular problems, sexual problems, possible causes of and options for treatment, etc. Furthermore, lifestyle counseling (about smoking, physical activity, and alcohol use), physical examination (body weight, blood pressure, and condition of the feet), chronic complications, and laboratory research will be reviewed. The laboratory work will provide values for the fasting glucose, HbA1_c_, creatinine concentration and clearance, lipid spectrum, and urine albumin/creatinine ratio (or albumin concentration)[18].

### The intervention

In addition to instruction for adhering to the prevailing guidelines for diabetes care as described in usual care, the primary care nurses in the intervention practices will receive information about the various components of the implementation strategy: (1) training in MI, (2) adapting the diabetes protocol to local circumstances, (3) introducing a social map for support of lifestyle change, and (4) practice tools for maintaining the training program (Additional file 1). The "diabetes protocol", "social map" and "MI training" will be components of the training program, which consists of 4 half-day training sessions spread over the 1st half year. Primary care nurses will attend these sessions in groups of 5 to 8 people outside the practice. The "practice tools" will be a component of the follow-up and will start after the training program. The implementation strategy will start in the first training session.

#### Motivational interviewing

Motivational interviewing (MI) will be introduced as a tool for behavior change. The MI counseling technique is patient oriented and suitable for brief office visits, and it can be used to improve patient adherence to diet, exercise, and smoking counseling in daily routine[36]. Since the MI technique plays an important role in our study protocol, we have described it in more detail in Additional file 2.

##### Content

The first step in MI is to set the agenda for the consultation together with the patient[36]. "Agenda setting" will be an issue to keep in the back of your mind from the very beginning of the first interview. The basic question here will be, "What are we going to talk about?" The patient will be encouraged to choose one or more key items in this agenda setting. This will make consultations more structured and will lead to a more concrete action plan. After this, the primary care nurse will assess the patient's current behavior and motivation for change by rating and exploring importance and confidence with respect to the chosen key items. She will do this by reflective listening, summarizing, asking open questions, scaling, supporting self-efficacy, rolling with resistance, expressing empathy, and developing discrepancy. If there is a need and sufficient motivation for change regarding one or more items, the primary care nurse will consult with the patient to select one item as the goal for behavior change.

##### Structure

The MI training will be developed in cooperation with a professional trainer, who will also tutor the complete training program. Activities will include group discussions and role plays on specific skills such as use of the ambivalence, supporting self-efficacy, and reflective listening. Video fragments created by a professional involved with MI will be shown, and some video recordings of primary care nurses will be discussed to learn about good and not-so-good points of lifestyle counseling. After each training session, the primary care nurses will have homework: they will study the theory from the training session and apply this theory to at least two patients with diabetes (cases). The instruction to the primary care nurse will be to write down the two consultations and to take these cases to the next training.

#### Protocol for diabetes care

The Dutch guidelines for type 2 diabetes mellitus give recommendations for diagnostics and management to patients with diabetes[18]. However, some recommendations, such as which tasks are to be delegated to primary care nurses and how long a diabetes consultation should last, will have to be adapted to each practice in a localized protocol. During the training, the differences and agreements of several diabetes protocols from general practices will be discussed with the primary care nurses in order to show that there is more than one way to carry out diabetes care.

#### Social map

Practical information will be needed in the practice, e.g., about local diet and exercise programs, so that patients can learn about these programs from the primary care nurse. They will be encouraged to set up a network for (1) contacting local dieticians to make appointments about referral and treatment plans, and (2) gathering local exercise programs and determining whether local government offices or other parties will fund exercise programs (leading to a social map). During the training, the social map will be discussed, and primary care nurses who already have a social map in the general practice will share their ideas with other primary care nurses who do not have a social map in their general practice.

#### Practice tools

The following educational and supportive tools will be distributed after the training program: a laminated instruction chart with counseling techniques, record keeping information, and recommendations for regular telephone follow-ups to patients with diabetes; a help desk for primary care nurses; and a follow-up meeting for primary care nurses. We will ask the primary care nurses to keep up a record of consultation data, such as the stage of change of the patient with regard to diet, physical activity, smoking, and alcohol. The record keeping, like the instruction chart, will be a useful and practical reminder during consultations. The trainer will advise the primary care nurses to monitor patients every 3 months according to the treatment guidelines, to do MI, and to follow up regularly by telephone, which will be every month for the 1st half year and will probably decrease after that.

The research team will function as a help desk; primary care nurses will be able to call the research team for information, who will follow up with three phone calls to inquire about the development of the primary care nurses' health counseling. The nurses' difficulties with the counseling technique will be mentioned to this team and they will look for solutions. When primary care nurses consider a follow-up meeting (an afternoon) important, this meeting will take p[lace. These supportive tools will be used in the follow-up period for maintenance of the MI training.

### Effect evaluation

The aim of the effect evaluation will be to determine whether the implementation strategy has achieved the intended effects on the care process and the patients' clinical outcomes. The research question will be, "What are the effects of an implementation strategy aimed at improving MI skills of primary care nurses compared to the effects of usual care on the care process, the metabolic parameters (such as HbA1_c_, blood pressure, and lipids), lifestyle (diet, exercise, smoking and alcohol consumption), health-related quality of life, and patients' willingness to change their behavior?"

#### Variables and measures

Figure 2 and Table 1 give a detailed overview of the outcome measures and instruments. The outcome measures will be the care process, the patients' metabolic parameters HbA1_c_, blood pressure, lipids [low-density lipoprotein (LDL) and total cholesterol], lifestyle (diet, exercise, smoking, and alcohol consumption), health-related quality of life, and the patients' willingness to change their behavior. Working with MI and diabetes check-ups carried out by primary care nurses will provide the two measures of the care process. Data about the degree to which the nurses work according to the MI principles will be obtained from the record keeping, and data from medical files will help us gain insight into the diabetes check-ups. The metabolic parameters will be obtained from medical files. The current state of the art in measuring lifestyle changes is a multi-method approach that combines feasible self-reporting and reasonably objective measures. The patients will also report specific behaviors relating to smoking[37], saturated fat intake[38], fruit and vegetable consumption[39], physical activity[40,41] and alcohol use[42] by means of validated self-reported questionnaires. We will use an objective measurement, the personal activity meter (PAM), with a diary for recording physical activity for 7 days. A combination of subjective and objective reporting will be chosen to get insight into the amount of exercise. A self-reported questionnaire will be used to measure the health-related quality of life[43,44] and the patients' willingness to change their behavior. This willingness to change will be determined on the basis of answers to questions about the importance and the confidence to change. Other factors that will be recorded include background characteristics about the patient (sex, education, etc.), the nurse (sex, age, etc.) and the general practice (year of establishment, consultation characteristics, etc.).

**Table 1 T1:** Effect evaluation: outcome variables and instruments used to measure them

**Outcome variables**	**Dutch guideline norms**	**Instruments**

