**Care process**		
Effects of MI	-	Record keeping
Results of diabetes check-ups	-	Medical files
		

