#### Data analysis

We will explore the influences on the model introduced by differences in the primary care nurses' accurate performance of MI. Video recordings of diabetes consultations in the intervention and control arms will be scored with the existing checklist, the BECCI, to determine the extent to which the MI technique was implemented[46]. Descriptive statistics will be used to summarize the patients' opinions of the diabetes consultations and the nurses' opinions of the feasibility of the implementation strategy.

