We assume that getting the practice motivated for structured care will not be very difficult, if they can get some support from us for making their schedules. We also assume that it will be easy to motivate the primary care nurse to use the MI tool because an effective tool for discussing diet and exercise is currently not available in general practice. However, the nurses will have to be supported in their motivation to participate, especially in the long run. Some suggestions from the literature that we have already elaborated on in our intervention strategy are MI training followed by a follow-up meeting, an instruction chart with counseling techniques, a record keeping system for consultation data and behavioral change, and regular telephone follow-ups to the primary care nurses. These items can be helpful in maintaining motivation, as well as getting feedback about the results[59].

In contrast to these assumes, we think that it is very difficult to receive the records of the nurses in order to establish the actual usage of MI. We will provide effort to get the records of all primary care nurses, because these records are very useful.

Furthermore, we expect that there will be more effects on lifestyle outcome measures than on metabolic parameters because a lifestyle change must occur before we can measure an effect on metabolic parameters. We expect the metabolic parameters to have stronger long-term effects.

Although we originally intended to use more objective measures for the outcome measurements of the effect evaluation, logistic and financial conditions often preclude this. A biomarker for fruit and vegetables, such as carotene measurement, is expensive. There is no simple biomarker available for alcohol. The influence of information bias resulting from subjective self-reports can be reduced in the data analysis by taking the use of pre-intervention scores (which have the same information bias) into account. We will make use of practicable objective measurements of physical activity. Personal activity meters are known not to register all activities with accuracy, and the level of activity can vary from week to week, but we have chosen to combine subjective and objective data to get better insight into the amount of exercise. There are a great many different actometers in circulation. We have chosen an accelerometer, which is more accurate than the pedometer that counts the number of steps walked in a day[60,61].

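### One of the two care-process measures, use of motivational interviewing (MI), is tied to a record that only trained intervention nurses are described as keeping, although BECCI scores from both arms are already planned

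*Protocol article*

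**What the plan says.** Research question 1(a), repeated under Effect evaluation, is a comparison with usual care on the care process. Variables and measures defines that outcome: "Working with MI and diabetes check-ups carried out by primary care nurses will provide the two measures of the care process". The sources differ. For MI: "Data about the degree to which the nurses work according to the MI principles will be obtained from the record keeping". For check-ups: "data from medical files will help us gain insight into the diabetes check-ups". Table 1 agrees and gives "Record keeping" as the only instrument for the MI row.

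The section The intervention lists practice tools as the fourth component of the strategy for intervention practices, starting once training is over. The section Practice tools repeats the timing, "The following educational and supportive tools will be distributed after the training program", and places record keeping among those tools. Its example of content is the patient's stage of change for diet, activity, smoking and alcohol. On the other arm, Control group conditions/usual care says: "The primary care nurses in the control group will not have access to the implementation strategy".

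The process evaluation has a separate instrument. Each nurse records 8 to 10 consultations before and after the trial, and its Data analysis section says: "Video recordings of diabetes consultations in the intervention and control arms will be scored with the existing checklist". That checklist is the BECCI, which appears in Table 2 and not in Table 1.

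**The concern.** An outcome meant for comparison between arms needs an instrument that exists in both. Here the instrument for MI use is itself part of the intervention. It is handed out to one arm, after the point at which a baseline would be taken, and is completed by the nurses being evaluated. It also serves as a reminder during consultations, so keeping the record is part of the treatment. Its one described content item concerns the patient's readiness to change, which is not a rating of how the nurse conducted the interview.

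At stake is the first step by which training could reach patients: whether nurses consult differently from their usual-care colleagues. If patient outcomes show no difference, a pre-stated arm contrast in MI use helps to separate training that did not take hold from a method that did not work. With the outcome tied to record keeping, the plan names no such contrast in its effect evaluation.

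**Working it through.** The plan states no figure on this point, so the check is mainly a tracing of sources.

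**1. Availability of each instrument, as described**

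| Instrument | Control arm | Baseline | After training | Where described |
|---|---|---|---|---|
| Record keeping (MI, Table 1) | none described | none described | intervention arm | The intervention; Practice tools |
| Medical files (check-ups, Table 1) | yes | yes | yes | Variables and measures; Timing of measurements |
| Consultation recordings scored with BECCI (Table 2) | yes | yes | yes | Process evaluation |

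Only the first row lacks a comparator and a baseline, and it is the row assigned to MI under question 1(a).

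**2. Does the two-arm data collection fill the gap?** Timing of measurements lists, for both arms at T0 and T1, medical-file data, questionnaires, the activity meter and its diary. The recording forms it mentions are for extracting medical-file data and are a different thing from the nurses' consultation record. Nurse record keeping is not listed. This is supporting evidence only, because the consultation recordings are not listed there either; they are described under the process evaluation.

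**3. Size of the gap.** By inference, the named MI instrument covers 0 of 35 control practices at any time and 0 of 70 practices at T0.

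**4. Volume of the alternative.** With one nurse in each of 70 practices:
- 70 × 8 = 560 and 70 × 10 = 700 recordings per set.
- If 8 to 10 are made at each time point, 2 × 560 = 1,120 to 2 × 700 = 1,400.
- The wording also allows 8 to 10 in total over both occasions, which gives 560 to 700. The plan does not settle which is meant.

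**5. What the BECCI comparison could detect (illustration).** Take one mean score per nurse, 35 nurses per arm, two-sided alpha 0.05, power 80%, and the normal approximation:

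standardised difference = (1.960 + 0.842) × √(2/35) = 2.802 × 0.239 = 0.67 SD.

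This is before baseline adjustment, which would improve it, and before loss of recordings, which would worsen it. The plan gives no expected BECCI difference to set against this figure.

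**The case against.** The strongest reply is that nothing is lost. MI use is measured in both arms, before and after, with a published checklist, and the process evaluation says it will examine how well nurses applied MI. On this view the fault is one of labelling: the right instrument sits in Table 2 instead of Table 1. Much of this stands, and it is why the severity is moderate. It does not remove the fault. The article names the instrument for this outcome twice, in the text and in Table 1, and both times names one that cannot deliver the comparison. The stated uses of BECCI are to describe implementation and to explore its influence on the model; a baseline-adjusted contrast between arms is not stated.

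Other replies limit how far the point can go:

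- No sentence says that control nurses keep no records. That is inferred from three sections read together. The inference is strong, but it is an inference.
- Record keeping might be loose wording for the video recordings. Tables 1 and 2 list them as different instruments, so the text would still need correction.
- The Discussion says "we think that it is very difficult to receive the records of the nurses" when the aim is to establish actual MI use. This may refer to the recordings. It therefore cannot be held against record keeping alone, and it may be a warning about the alternative.

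A reader might infer three stronger things that the documents do not support. First, that question 1(a) as a whole has no control or baseline data; check-ups from medical files have both. Second, that the trial could not show a change in nurse behaviour; the BECCI scores could show it. Third, that the planned regression breaks down for this outcome. The Data analysis section introduces its two-level logistic model after dichotomising patient outcomes, Table 1 gives the care process no norm, and the article never clearly assigns that model to a nurse-level MI measure.

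**Conclusion.** The point holds for the MI half of question 1(a). The only instrument named for it is described solely as a post-training tool of the intervention arm, so it cannot support a comparison with usual care. The conclusion rests on reading record keeping as the practice tool of that name, which the two tables support, and on control nurses not keeping the same record, which follows from their exclusion from the strategy. Since the article itself fixes the instrument, this is a poor stated choice and not a detail left to a fuller document.

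Severity is moderate. One of two care-process measures is affected; no patient outcome, sample size or error rate is touched; and suitable data are already planned in both arms.

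**What to change.** In Variables and measures and in the MI row of Table 1, replace record keeping with the BECCI score from the before-and-after consultation recordings as the between-arm measure of MI use. State the comparison: post-trial score by arm, adjusted for the nurse's pre-trial mean score, with practice as the cluster. Say whether 8 to 10 recordings are meant per occasion or in total. Where feasible, score recordings in random order with arm and time point hidden from the scorer. Keep record keeping as an intervention-arm description of uptake.

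The cost is small. Recordings and scoring in both arms are already planned; the new work is the organisation of masked scoring. The main risk is incomplete return of recordings, which the Discussion may already anticipate. Report the number of nurses and recordings obtained by arm and time point, so that a reader can judge whether the comparison is distorted by who sent them in.

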**Care process**		
Effects of MI	-	Record keeping
Results of diabetes check-ups	-	Medical files
		
**Metabolic parameters**		
HbA1_c_	< 7%	Medical files
Blood pressure	< 140 mm Hg	Medical files
Lipids:		
LDL	< 2.5 mmol/L	Medical files
Total cholesterol	< 4.5 mmol/L	Medical files
		
**Lifestyle**		
Diet:		
Fruit and Vegetables	2 pieces fruit (200 g or more) and 200 g vegetables or more	Validated questionnaire, 8 items [39]
Fat consumption	Total fat < 35 energy percent Saturated fat < 10 energy percent	Validated questionnaire, 35 items [38]
Physical activity	30 min for 5 days/week	Questionnaire, modified Dutch version of the CHAMPS, unvalidated, 15 items [40,41]
		Personal activity meter with diary for 7 days
		
Smoking	No smoking	Validated questionnaire, 2 items [37]
Alcohol consumption	Man: maximum 2 glasses	Validated questionnaire, 2 items [42]
	Woman: maximum 1 glass	
		
**Quality of life**	-	Validated questionnaires, EQ-5D 5 items and VAS 1 item [43,44]
		
**Patients' willingness to change behavior**	-	Questionnaire

**Figure 2 F2:**
[figure not shown]
**Flowchart showing relationship of the strategy, characteristics, variables, and indicators**.

#### Timing of measurements

Information will be collected before intervention starts (T0), as well as at the end of the trial 14 months later (T1) for the intervention and control arms:

- At T0 (baseline), the research team will collect data from medical files, such as HbA1_c _concentration, blood pressure, and lipid values. Eligible patients will receive the first questionnaire from our research team (with a invitation letter from the GP) to assess their lifestyle and quality of life. Primary care nurses will instruct participating patients to carry a personal activity meter for 1 week, and to keep a diary, noting his/her physical activity for that week.

- At T1, the second and final questionnaire, PAM and diary will be sent to the patient's home address. The primary care nurse will collect data from medical files regarding medical parameters from the most recent patient contact.

The questionnaires, personal activity meters, diaries, and recording forms for medical file research are to be sent to the research team in a postage-paid envelope after completion. All these materials will carry a unique patient number, and the patient number will be related to the involved general practice number.

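### At T1 the nurse, who knows her arm, abstracts the metabolic outcomes from the latest contact, which may hold no HbA1c, blood pressure or lipid value

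*Protocol article*

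**What the plan says.** The metabolic outcomes are HbA1c, blood pressure, LDL and total cholesterol. They come from routine records (Variables and measures): "The metabolic parameters will be obtained from medical files".

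The Timing of measurements section assigns the abstraction to different people at the two time points:

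- Baseline: "At T0 (baseline), the research team will collect data from medical files".
- Fourteen months later: "The primary care nurse will collect data from medical files regarding medical parameters from the most recent patient contact". The "recording forms for medical file research are to be sent to the research team" by post. The section gives no limit on how old a T1 value may be and describes no masked abstraction or check.

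The nurse is the person the strategy is aimed at. Intervention nurses are trained (The intervention), and for the others "The primary care nurses in the control group will not have access to the implementation strategy" (Control group conditions/usual care).

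On what each contact yields, the Three-monthly check-ups section lists weight and adds: "The fasting blood glucose value will also be determined every 3 months". HbA1c and the lipid spectrum appear under Annual check-ups, in the sentence that begins "The laboratory work will provide values for the fasting glucose". Blood pressure is also listed only there. Under Practice tools, intervention nurses are further advised to telephone patients monthly for the first half year and probably less often after that.

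**The concern.** An outcome rule should return the same quantity in both arms whoever applies it. This one may not, for three reasons.

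- The abstractor changes between T0 and T1, although the T0 value is the covariate in the model. The T1 abstractor knows the allocation, and her own care is under test.
- The rule names a contact, not a measurement. If that contact has no HbA1c, blood pressure or lipid result, the rule gives either a blank or an unmasked choice of how far back to look.
- Contacts can differ by arm, because the telephone calls are advised only in the intervention arm and a call need not produce any measurement.

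Patients enter with a latest HbA1c above 7.0% (Patients), and success is a value below 7% (Data analysis, Effect evaluation). If there is no newer test and the qualifying value is carried forward, the patient counts as a failure by construction. If one arm is retested more often, regression to the mean alone could then produce a difference.

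HbA1c drives the first sample-size calculation and is named as the primary outcome measure of the economic evaluation, so this rule bears on a main result.

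**Working it through.** The plan gives no figure for this point, so there is none to reproduce. The check is a comparison of sections followed by calendar arithmetic.

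**1. Does the latest contact hold the outcome?** Study design refers to four guideline appointments. If one of the four is the annual check-up, then 3/4 = 75% of regular contacts have no HbA1c, lipid or blood pressure entry on the listed schedule. The eligibility text itself says only that the latest HbA1c is frequently, not always, within the past year.

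**2. How old can a T1 HbA1c be?**

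Inputs from the article:
- Training starts in month 4, and follow-up data are collected in months 18–25 (Time frame).
- Training is spread over half a year (The intervention).

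Assumptions:
- The half year runs from the start of training, so training ends at about 4 + 6 = month 10.
- HbA1c is tested once a year, and the age of the last test is uniform over 0–12 months.
- Extraction is uniform over months 18–25.

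For extraction in month T, the share of values dated before month m is max(0, 12 − (T − m))/12.

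- End of training (m = 10), T = 18: 4/12 = 33%. From T = 22 on: 0%.
- Average over eight monthly points: (4 + 3 + 2 + 1 + 0 + 0 + 0 + 0)/(8 × 12) = 10/96 = 10.4%.
- Average in continuous time: (4²/2)/(12 × 7) = 8/84 = 9.5%.
- Follow-up meeting (m = 12): 6/12 = 50% at T = 18, and on average (6²/2)/(12 × 7) = 18/84 = 21%.
- Oldest possible annual value: month 18 − 12 = 6 to month 25 − 12 = 13, so always after month 4.

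Sensitivity to the assumptions:
- Six-monthly testing: the oldest value at T = 18 is from month 12, so 0% predate month 10.
- Training over by month 9: (3²/2)/(12 × 7) = 4.5/84 = 5%. Training over by month 6: 0%.
- T1 exactly 14 months after a month 1–7 baseline, i.e. months 15–21 with mean 18: (22 − 18)/12 = 33%. This is not the collection calendar that the article sets out.

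**3. What would that dilution cost?** As an illustration, take the plan's own proportions (48% against 24%), its intracluster correlation of 0.05, a two-sided 5% test, and no effect at all in values that predate the end of training.

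- Diluted proportion: 24% + 24% × 0.095 = 26.3%.
- 30 practices × 5 patients per arm: effective n = 150/(1 + 4 × 0.05) = 125. Power falls from 98% to 95%.
- 35 practices × 10 patients per arm: effective n = 350/(1 + 9 × 0.05) = 241. Power falls from above 99.9% to 99.9%.
- With the month-12 cut (21%), the proportion is 29.1%, and power is 87% and 99% respectively.

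**4. What cannot be computed.** The article gives no retest frequency, completeness or contact pattern by arm. The difference that selective look-back or unequal missingness could produce therefore has no size or direction that can be derived from it.

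**The case against.** The case on the other side is substantial, and much of it stands.

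- *The rule is fixed and the results are recorded.* The nurse transcribes, and HbA1c and lipids are laboratory values. A reader might infer that she is free to pick results, or that the outcome is biased. The text supports neither. Her discretion arises only where the named contact holds no value.
- *Annual-only testing is an inference.* The schedule is introduced for patients without complaints and with good regulation, whereas trial patients have HbA1c above 7.0% and may be tested more often. The article does not say. It also sets follow-up at 14 months, which should span an annual check-up.
- *Three-monthly monitoring is not specific to the intervention.* A reader might take the line "The trainer will advise the primary care nurses to monitor patients every 3 months according to the treatment guidelines" as an arm difference, but the usual-care section gives the same interval. Only the telephone calls differ, and they are expected to become less frequent before T1.
- *Old values do little harm on average.* It is tempting to say that a third of T1 values predate the end of training. On the article's calendar that holds only for extraction in month 18. On that calendar and with annual tests, no value predates the start of the strategy in month 4.
- *A condensed article may omit details of the form.* Whether the form records dates is indeed not a finding. Who abstracts, and from which contact, is stated, and that is the point raised here.

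These arguments limit the size of the problem. They do not repair a rule that can point to an empty contact and leaves the resolution to someone who knows the arm.

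**Conclusion.** The point holds as a flaw in a stated rule. The abstractor changes between baseline and outcome, the T1 abstractor is necessarily unmasked, and the contact she is told to use may hold none of the outcomes. What follows is a risk of selection and missingness that differ by arm, including carry-forward of the qualifying HbA1c. The article does not show that bias occurs, nor in which direction.

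The part that can be sized is small: about 10% of T1 HbA1c values would predate the end of training, with a range of 0% to 33% depending on testing interval, extraction month and when training ends. That rests on annual, uniformly spread tests and training ending at about month 10. Loss of power is therefore not the reason to act. The reason is that unmasked, possibly arm-dependent ascertainment cannot be corrected in the analysis if measurement dates are not kept.

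**What to change.** In Timing of measurements, replace the T1 instruction with a dated listing and one masked selection rule:

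1. The practice returns a form, or a file or laboratory printout, with every dated HbA1c, blood pressure and lipid value since T0.
2. A research team member masked to arm makes the selection. That person should not work on the help desk or the calls to nurses, which Practice tools assigns to the research team.
3. The selected value is the last one on or before the patient's T1 date, by the same rule in both arms. The look-back is wide enough to cover an annual test. Any value dated on or before T0 is excluded and counts as missing.
4. Measurement dates and completeness are reported by arm. A sensitivity analysis is limited to values dated after training ended, with the same calendar cut in control practices, or to a narrower window.

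A narrow window should not be the main rule. With annual tests spread uniformly, ±3 months would capture only 6/12 = 50% of patients.

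The cost is slightly more form work and some values missing instead of stale. The change concerns abstraction only and leaves patient care as it is.
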